#### Primary outcome

2.4.1

The primary outcome of this study is the ratio of EN energy intake to the prescribed target energy on Day 5 after randomization. Patients who died before Day 5 will not be included in the analysis of the primary outcome. Patients who were discharged from ICU before Day5 will be followed up after ICU discharge.

Target energy requirements will be estimated using a simple weight-based equation of 25 kcal/kg of body weight. Body weight used for calculating energy requirements will follow the recommendations of the 2023 ESPEN guideline (2): actual body weight will be used if the body mass index (BMI) is ≤25. For patients with BMI > 25, an adjusted body weight will be applied, defined as:

Adjusted body weight = Ideal body weight + 25% × (actual body weight–ideal body weight). Ideal body weight (kg) will be determined using the formula: 0.9 × height (cm)–100 for males, and 0.9 × height (cm)–106 for females.

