### Data collection and management

2.5

Data will be collected and stored using a secure, web-based electronic data capture system (Unimed Science Inc., Wuxi, China). At each participating center, the principal investigator will be responsible for oversight of patient enrollment and data entry. Data entry will be performed exclusively by the principal investigator or by up to two designated research staff members authorized by the principal investigator.

Standardized training in data entry and database use will be provided by the database vendor in collaboration with the CCCNTG coordinating center. All data required to characterize baseline patient characteristics (Table 1), study and control interventions, potential confounding co-interventions, and study outcomes will be systematically and prospectively collected in accordance with the study protocol. Table 2 shows the schedule of enrolment, interventions, and main data collected.

**TABLE 1 T1:** Baseline characteristics of patients by treatment group.

Characteristics	Pectin group (*n* = xx)	Control group (*n* = xx)
Age, years		
Male gender, no. (%)		
BMI, kg/m^2^		
Admission diagnosis, no. (%)		
Respiratory		
Cardiovascular		
Gastrointestinal		
Neurological		
Sepsis		
Trauma		
Others		
ICU source of admission, no. (%)		
Emergency		
Medical		
Surgical		
Others		
Comorbidities, no. (%)		
Hypertension		
Coronary disease		
Diabetes		
Chronic respiratory diseases		
Stroke		
Gastrointestinal disease		
Malignant tumor		
Others		
Interval from ICU admission to randomization, days		
APACHE II score		
SOFA score		
mNUTRIC score		
Presence of organ failure at baseline, no. (%)		
Respiratory		
Renal		
Cardiovascular		
Organ support at baseline, no. (%)		
Renal replacement therapy		
Vasoactive drugs		
Serum albumin, g/L		
Serum creatinine, μmol/L		
BUN, mmol/L		
CRP, mg/L		
PPIs use before randomization, no. (%)		

BMI, body mass index; ICU, intensive care unit; APACHE II, Acute Physiology and Chronic Health Evaluation II; SOFA, Sequential Organ Failure Assessment; mNUTRIC, modified Nutrition Risk in the Critically Ill; BUN, blood urea nitrogen; CRP, C-reactive protein; PPI, proton pump inhibitor.

**TABLE 2 T2:** Schedule of enrolment, intervention, and data collection.

	Study period									
Time point	Screening	Randomiza-tion	After randomization/day							End
		0	1	2	3	4	5	6	7	28
Enrollment										
Eligibility screen	×	–	–	–	–	–	–	–	–	–
Informed consent	×	–	–	–	–	–	–	–	–	–
Allocation	–	×	–	–	–	–	–	–	–	–

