### Sample size estimation

2.6

Based on a previous nationwide multicenter trial (the NEED trial) conducted by the CCCNTG (19), among patients receiving invasive mechanical ventilation, the mean (standard deviation) ratio of EN energy intake to the prescribed target energy on Day 5 was 62.9% (31.1%) in the control group. Assuming a minimal clinically meaningful relative increase of 20% in the intervention group, with 80% power, a two-sided alpha of 0.05, and a 1:1 allocation ratio, the required sample size is 96 participants per arm (PASS ver.11.0; NCSS, LLC). To account for potential attrition, including withdrawal or dropped, estimated at approximately 10%, the final sample size was increased to 212 participants (106 per group).

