Statistical methods: Normality of continuous variables will be assessed using the Shapiro-Wilk test. Normally distributed continuous variables will be summarized as mean ± standard deviation and compared using Student’s *t*-test; non-normally distributed variables will be summarized as median (interquartile range, IQR) and compared using the Mann-Whitney U test. Categorical variables will be summarized as counts and percentages and compared using Pearson’s chi-square test. Effect estimates with 95% confidence intervals (CIs) will be reported throughout. No adjustment for multiple comparisons will be applied; all secondary outcome analyses are considered exploratory and hypothesis-generating. For secondary outcomes, complete-case analysis will be used, with missing data rates reported for each outcome. A two-sided *P*-value < 0.05 will be considered statistically significant.

Subgroup analyses: Pre-specified subgroup analyses will be conducted according to the following baseline characteristics: age (>60 vs. ≤59 years), BMI (>25 vs. ≤25 kg/m^2^), SOFA score (≥9 vs. <9), and ICU admission type (emergency, surgical, medical, or other).

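### The primary Day-5 EN ratio is compared without baseline covariates or site, which gives up available precision, although the planned test is valid and the sample size reproduces

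*Protocol article*

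**What the plan says.** Primary outcome section: "The primary outcome of this study is the ratio of EN energy intake to the prescribed target energy on Day 5 after randomization". This is a continuous variable.

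Data analysis section, statistical methods: "Normally distributed continuous variables will be summarized as mean ± standard deviation and compared using" Student's t-test. If Shapiro-Wilk rejects normality, medians are reported and a Mann-Whitney U test is used. The paragraph on the primary outcome in the same section deals with deaths before Day 5 and missing data and names no model. No adjusted analysis appears, even as a sensitivity analysis.

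Baseline information is nevertheless collected: "All data required to characterize baseline patient characteristics (Table 1") are to be recorded prospectively, and Table 1 lists age, BMI, SOFA, APACHE II and baseline vasoactive drugs. Age, BMI and SOFA are used only to define subgroups (for example "SOFA score (≥9 vs. <9), and ICU admission type"). Section 2.2 stratifies randomization by site, but site does not enter the analysis.

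The denominator of the ratio depends on weight: "Target energy requirements will be estimated using a simple weight-based equation of 25 kcal/kg of body weight". The body weight used changes from actual to adjusted when BMI exceeds 25.

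**The concern.** When baseline variables predict the outcome, a two-sample test leaves the variation they explain in the error term. A linear model removes it, narrows the confidence interval and corrects the estimate for the imbalance that happened to occur. It needs no extra patients. Ignoring the stratification factor has a second effect: if sites differ in EN delivery, the t-test overstates the standard error and becomes conservative.

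This matters here because the calculation behind 96 per arm meets its 80% target with nothing to spare.

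One link to the outcome comes from the protocol's own formula. For a man of 170 cm, ideal weight is 0.9 × 170 − 100 = 53 kg. At BMI 25 he weighs 72.25 kg and his target is 25 × 72.25 = 1,806 kcal. Just above BMI 25 the weight used is 53 + 0.25 × 19.25 = 57.8 kg and the target is 1,445 kcal, 20% lower. For the same energy delivered, the ratio would be about 25% higher in relative terms. This is an upper illustration, because section 2.3.3 sets the infusion rate to meet the energy requirement, so intake should partly follow the target.

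**Working it through.** **Inputs (Sample size estimation section).** The Day-5 ratio, as mean and SD, "was 62.9% (31.1%) in the control group". The effect sought is a 20% relative gain, so the difference is 0.20 × 62.9 = 12.58 points. Power is set at 80%, alpha at 0.05 (two-sided), and the arms are of equal size.

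**The plan's own figure.** n per arm = 2 × (1.960 + 0.842)² × (31.1/12.58)² = 95.9, so 96. It reproduces. Power at 96 per arm is 80.0% by the normal approximation and 79.6% by the noncentral t distribution.

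**With adjustment.** Residual SD = 31.1 × √(1 − R²). Power is from the noncentral t at 96 per arm. Equivalent extra patients = 192 × (1/(1 − R²) − 1). R² is assumed.

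| R² | Residual SD | Power | Equivalent extra patients |
|---|---|---|---|
| 0 | 31.10 | 79.6% | 0 |
| 0.02 | 30.79 | 80.4% | 4 |
| 0.05 | 30.31 | 81.6% | 10 |
| 0.10 | 29.50 | 83.6% | 21 |
| 0.20 | 27.82 | 87.6% | 48 |

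**Cost of estimating the coefficients.** The table treats the covariates as balanced between arms. Five patient-level terms (age, BMI, BMI > 25, SOFA, vasoactive use) inflate the variance by about 5/(192 − 5 − 3) = 2.7% on average through chance imbalance. That roughly cancels an R² of 2 to 3%. Net power is then about 79.4%, 80.6%, 82.6% and 86.8% for the four assumed R² values. Site terms add little to this, because the randomization balances them.

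**Site.** If site explains 5% or 10% of the variance (assumed), the t-test that ignores it has a true type I error of 2 × (1 − Φ(1.960/√(1 − share))), which is 4.4% or 3.9% against the nominal 5%. By the normal approximation, power is 80.6% or 81.3% without site and 82.0% or 84.0% with it.

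**Chance imbalance.** The probability that a given covariate differs by more than 0.2 SD between arms is 2 × (1 − Φ(0.2/√(2/96))) = 16.6%. At an assumed correlation of 0.3 with the outcome, a 0.2 SD imbalance moves the unadjusted difference by 0.2 × 0.3 × 31.1 = 1.9 points. That is 15% of 12.58, and less than half the unadjusted standard error of 31.1 × √(2/96) = 4.5 points.

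**Scope.** These figures compare with the t-test only. No gain over the Mann-Whitney branch has been computed.

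**The case against.** The strongest reply is that nothing here is wrong. The sample size is for an unadjusted comparison of two means, and the analysis is that comparison. Under randomization the test is valid, and its error rate and confidence interval already allow for chance imbalance. All of this stands. A reader might infer that the planned analysis is biased or the sample size miscalculated, but the documents support neither.

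The size of the benefit is also assumed. Listing a variable as a subgroup factor concerns variation in the treatment effect and does not show prognostic strength; vasoactive use is not a subgroup factor at all. Dividing by a target that the infusion rate is meant to follow already removes part of the effect of weight. This stands too, which is why the range starts at 2%.

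The lack of reserve describes 96 per arm, the number left after planned attrition. If all 106 per arm were analysed, unadjusted t-test power would be 83.4%.

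Finally, a separate SAP may exist, and covariate lists often sit there. The missing list alone would be no finding. But the article does not leave the test open: it states two unadjusted tests for continuous variables and offers no other for the primary outcome. That these tests apply to the primary outcome is an inference, and the natural one. It should not be stretched to every continuous outcome, since time to ICU and hospital discharge are assigned to Fine-Gray models.

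**Conclusion.** The point holds as a loss of efficiency. As written, the primary comparison uses neither the collected baseline variables nor the stratification factor. The power forgone at 96 per arm is nil to negligible if the covariates explain about 2% of the variance, roughly 1 to 2 points at 5%, 3 to 4 at 10% and 7 to 8 at 20%. The lower figure in each range allows for estimating the coefficients. If the explained variance lies mainly between sites, the gain over the planned test is smaller (1.4 to 2.7 points for 5 to 10%), but the test also stops being conservative.

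These sizes rest on an R² that the documents do not give. The only link they establish themselves is the change in the target-weight formula at BMI 25; the prognostic value of SOFA, vasoactive use and age is an assumption. The change is worth making because it costs little. The trial remains valid without it.

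**What to change.** In section 2.7, make the primary comparison a linear model of the Day-5 ratio on arm, with robust standard errors and these terms: site, age, BMI (continuous plus an indicator for BMI > 25, because the denominator changes form there), pre-randomization SOFA and baseline vasoactive use. Report the adjusted mean difference in percentage points with its 95% CI. Keep the unadjusted comparison as supportive.

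Before unblinding, fix three things:

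- The covariate list. Keep it short, since each weak covariate costs precision.
- The SOFA time point. Table 1 lists SOFA as a baseline characteristic, but Table 2 schedules the score only on Days 1 to 7. A value affected by treatment must not be used as a covariate.
- A simple rule for missing covariates that ignores treatment arm.

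The cost is protocol or SAP wording, a few degrees of freedom and minor extra analysis work. No patients are added, and no new variables provided the baseline SOFA in Table 1 is recorded before randomization.

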Pectin, a gelatinous substance derived from the cell walls of fruits and plants, is a major component of water-soluble dietary fiber and possesses multiple biological activities. In the acidic gastric environment, pectin can interact with calcium ions (Ca^2+^) to form a semi-solid gel (12, 13). Increasing the viscosity of EN with pectin may therefore reduce diarrhea and reflux aspiration risk (14). A systematic review and meta-analysis showed that pectin-supplemented EN was associated with reduced diarrhea, fewer infectious complications, and a shorter length of stay (15). Notably, its effect was evident in patients not receiving proton pump inhibitors (PPIs) but absent in those on PPIs (16), likely because conventional pectin requires an acidic environment to gel. Low-esterified pectin, however, can form a stable hydrogel even under low-acid conditions, via a pH-independent Ca^2+^-mediated gelation mechanism (17), thereby increasing intragastric content cohesiveness and reducing retrograde flow and reflux-driven interruptions. This distinguishes our intervention from generic fiber supplementation and broadens its applicability to the general critically ill population.

Although pectin supplementation appears promising in reducing feeding intolerance and improving clinical outcomes, most existing evidence comes from observational studies or small, single-center randomized controlled trials (RCTs). To address this gap, we plan to conduct a multicenter RCT (PROMOTE trial). Our hypothesis is that EN supplemented with low-esterified pectin, a physiochemically more robust form of pectin, will improve feeding tolerance and enable greater total energy delivery compared with usual care in critically ill adults.

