#### Inclusion criteria

2.1.1

1. Aged ≥ 18 years old;

2. Admitted to ICU < 24 h;

3. Receive invasive mechanical ventilation < 72 h, and the expected duration of continued treatment > 48 h;

4. Do not expect to feed orally for more than 3 days and plan to receive gastric feeding;

5. No operation plan within a week;

6. Informed consent form obtained from the patient or next of kin.

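### The age subgroup cut leaves 60-year-olds in neither group, and the subgroup list omits baseline PPI use, which the Introduction discusses as an effect modifier and Table 1 already collects

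*Protocol article*

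**What the plan says.** Section 2.7 (Data analysis, Subgroup analyses) names four baseline characteristics as the pre-specified subgroups:

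- age: "age (>60 vs. ≤59 years")
- body mass index: "BMI (>25 vs. ≤25 kg/m^2")
- organ failure score and admission type: "SOFA score (≥9 vs. <9), and ICU admission type (emergency, surgical, medical, or other")

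PPI use is not among them. Eligibility under section 2.1.1 is "Aged ≥ 18 years old", with no upper limit, so patients aged 60 can be enrolled.

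The Introduction says of earlier pectin-supplemented feeding that "its effect was evident in patients not receiving proton pump inhibitors (PPIs) but absent in those on PPIs", and attributes this to conventional pectin needing acid to gel. Of low-esterified pectin it says that it "can form a stable hydrogel even under low-acid conditions, via a pH-independent Ca^2+^-mediated gelation mechanism", and concludes: "This distinguishes our intervention from generic fiber supplementation and broadens its applicability to the general critically ill population". Table 1 in section 2.5 has a baseline row for "PPIs use before randomization, no". (%).

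**The concern.** There are two separate matters.

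The first is a gap in a stated rule. The two age categories do not meet, so some eligible patients have no category. The age subgroups would then not add up to the analysed total, and someone would have to decide later, possibly with data in hand, where those patients go.

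The second is a mismatch between rationale and subgroup list. PPI use is the only effect modifier for which the article itself cites evidence, and the choice of product is argued partly on its escaping that modification. The article gives no pectin-specific reason for any of the four listed subgroups. If nobody specifies a PPI comparison before unblinding, any later look at whether the effect persists on PPIs would be post hoc, although the baseline variable has been collected from the start.

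**Working it through.** **Age cut.** Set the categories side by side.

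| Subgroup | Upper category | Lower category | Value in neither |
|---|---|---|---|
| Age, whole years | >60 | ≤59 | 60 |
| Age, if held as a decimal | >60 | ≤59 | 59 < age ≤ 60 |
| BMI | >25 | ≤25 | none |
| SOFA | ≥9 | <9 | none |

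The BMI and SOFA cuts are exhaustive; the age cut is not. The documents give no age distribution, so the number affected rests on an assumed share aged 60:

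- 1%: 0.01 × 212 = 2.1 patients
- 2%: 0.02 × 212 = 4.2 patients
- 3%: 0.03 × 212 = 6.4 patients

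**Plan's own figure.** Inputs from section 2.6: control mean 62.9%, SD 31.1%, relative increase 20%, power 80%, two-sided alpha 0.05, allocation 1:1.

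- Difference: 0.20 × 62.9 = 12.58 percentage points.
- n per arm = 2 × (1.960 + 0.842)² × 31.1² / 12.58² ≈ 96, which matches the protocol.
- 96 × 1.1 ≈ 106 per arm, which is the stated figure (96 / 0.9 would give 107).

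The subgroup point does not touch this calculation.

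**What a PPI interaction could show.** Take N = 2 × 96 = 192 evaluable patients, and let q be the share on PPIs at baseline. The documents do not give q, so a range is assumed. With 1:1 allocation within each PPI stratum and a common SD:

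SE(interaction) = 31.1 × √(4/(N·q) + 4/(N·(1−q)))

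For q = 0.5: 31.1 × √(4/96 + 4/96) = 31.1 × 0.2887 = 8.98. The 95% CI half-width is 1.96 × 8.98 = 17.6. Power for a 12.58-point interaction (full design effect off PPIs, none on PPIs) is Φ(12.58/8.98 − 1.96) = Φ(−0.56) ≈ 0.29.

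| q (assumed) | SE | 95% CI half-width | Power for 12.58 points |
|---|---|---|---|
| 50% | 8.98 | 17.6 | 29% |
| 60% | 9.16 | 18.0 | 28% |
| 70% | 9.80 | 19.2 | 25% |
| 80% | 11.22 | 22.0 | 20% |
| 90% | 14.96 | 29.3 | 13% |

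The interaction detectable with 80% power runs from 25.2 points (q = 50%) to 41.9 points (q = 90%), that is, two to more than three times the whole design effect. With all 212 patients evaluable, the half-width would still be 16.7 to 27.9 points.

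**The case against.** **The age gap is a drafting slip.** The neighbouring cuts meet, only a few patients in one exploratory subgroup are involved, and the primary estimate, sample size and analysis populations are untouched. This stands. It limits the size of the point but does not remove the gap.

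**The PPI part asks for an addition.** The protocol promises no PPI subgroup, choosing subgroups is a design judgement, and an analysis plan not shown here could add one before unblinding. This also stands in part: the omission contradicts nothing in the protocol. The recommendation rests on fit with the trial's own rationale and on its low cost.

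**The rationale is that PPI status should not matter.** The Introduction ties the loss of effect on PPIs to conventional pectin and says the study product avoids it. The stated hypothesis, better feeding tolerance and greater energy delivery than usual care, does not mention PPIs. This is right, and it sets the purpose of the subgroup: to check whether the effect persists on PPIs.

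**Stronger readings to resist.** A reader might infer that without a PPI subgroup the trial cannot examine its mechanistic claim, or that a null overall result could not be interpreted. The documents do not support this.

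- A benefit in a population largely on PPIs would itself speak for applicability despite PPIs.
- Adding the subgroup would not rescue a null result, because the CI half-width exceeds the whole 12.58-point design effect at every share considered.
- One can compute a diluted overall effect of 12.58 × (1 − q), such as 6.3 points at q = 50% or 2.5 at q = 80%. That needs a PPI share the documents do not give and a zero effect on PPIs that the Introduction argues against for this product.

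**Baseline PPI use is an imperfect measure.** Patients are enrolled within 24 h of ICU admission, and Table 1 records use before randomization only, so PPIs started during the 7-day intervention are missed. This is a real limit. A baseline factor is nevertheless the right basis for a subgroup, because treatment cannot affect it.

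**Conclusion.** Both parts hold in limited form. The age cut is not exhaustive as written and should be corrected. It concerns about 2 to 6 of 212 patients if 1% to 3% are aged 60, and the primary analysis does not change. Baseline PPI use belongs in the list as an exploratory subgroup, because it is the modifier most closely tied to the article's rationale and needs no new data. Its yield is modest: about 13% to 29% power for a 12.58-point interaction and a CI half-width of about 18 to 29 points, assuming 90% to 50% on PPIs, 192 evaluable patients and the planning SD of 31.1 in every cell. It could inform the question of persistence on PPIs but not settle it. The shares aged 60 and on PPIs are assumptions throughout.

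**What to change.** 1. Make the age cut in section 2.7 exhaustive, for example ≥60 vs <60 years.
2. Before unblinding, add baseline PPI use (yes/no, from the Table 1 item) as a pre-specified exploratory subgroup. State that it checks persistence of effect on PPIs and that PPIs started after randomization are not captured.
3. Report each subgroup by a treatment-by-subgroup interaction estimate with 95% CI. Section 2.7 names only a t-test or Mann-Whitney test for continuous outcomes, so there is no adjusted primary model to extend. Use a separate regression with treatment, subgroup, their interaction and site.

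The cost is a wording amendment and one short additional model specification; no new data are needed. The downside is one more low-powered exploratory subgroup, which should be labelled as such.

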### Data and safety monitoring

2.8

An independent Data and Safety Monitoring Board (DSMB), comprising experts in clinical trials, biostatistics, and intensive care medicine, will be established to safeguard participant interests and monitor intervention safety throughout the trial. No formal interim efficacy analyses are planned. This decision was made at the protocol design stage and is consistent with the pragmatic nature of this trial. The DSMB will conduct safety reviews after every 50 participants complete the intervention, focusing on cumulative incidence of pre-specified SAEs, including intestinal ischemia, severe abdominal distension, and aspiration pneumonia and etc. The DSMB may recommend early termination on safety grounds at any time and the TMC will act on such recommendations within 48 h.

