### Study design, setting, and population

2.1

PROMOTE is a multicenter, open-label, randomized, parallel-controlled trial conducted by the Chinese Critical Care Nutrition Trials Group (CCCNTG). The trial will enroll 212 critically ill adult patients from ten intensive care units (ICUs) across China. Trial oversight will be provided by a Trial Management Committee (TMC), comprising the principal investigators from each participating center and key members of CCCNTG, which will be responsible for the overall conduct and coordination of the study. Recruitment started in February 2024 with competition for enrollment expected in 2026. The trial protocol was developed according to the Standard Protocol Items: Recommendations for Interventional Trials (SPIRIT) statement (18).

Patients aged ≥ 18 years and within 24 h of their index ICU admission will be screened for eligibility. Those requiring invasive mechanical ventilation and, therefore, unable to take oral nutrition, necessitating artificial nutritional support, will be eligible for inclusion. The complete inclusion and exclusion criteria are listed below:

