### Adverse events

2.9

Adverse events (AEs) are defined as any unfavorable medical occurrence in a study participant receiving the investigational intervention, regardless of its causal relationship to the intervention, in accordance with the National Cancer Institute Common Terminology Criteria for Adverse Events (NCI-CTCAE v5.0) (23).

Given the severity of underlying illness in critically ill patients, abnormalities in laboratory values, signs, or symptoms are common and will not automatically be classified as AEs unless they require clinically significant intervention or are considered clinically relevant at the investigator’s discretion. The underlying condition or diagnosis should be documented whenever possible (e.g., “acute kidney injury” rather than “hyperkalemia”).

AE assessment follows a two-level framework: (1) all-cause AE grading using NCI-CTCAE v5.0; and (2) the following pectin-specific adverse events of interest, which will be actively monitored throughout the intervention period:

a. Abdominal distension: clinical diagnosis based on physical examination and/or intra-abdominal pressure (IAP) ≥ 12 mmHg on routine bladder pressure measurement, corresponding to Grade I intra-abdominal hypertension (IAH) per the World Society of the Abdominal Compartment Syndrome (WSACS) consensus (24).

b. Enteral tube obstruction: inability to aspirate gastric contents or flush the tube with 20 mL warm water, necessitating tube replacement or unplanned cessation of enteral feeding.

c. Ileus: absence of bowel sounds on ≥3 consecutive assessments combined with cessation of stool passage and abdominal distension in the absence of mechanical obstruction, requiring clinical intervention.

d. Intestinal ischemia: radiologically or surgically confirmed bowel ischemia, or strong clinical suspicion based on rising lactate and unexplained hemodynamic deterioration, prompting urgent computed tomography (CT) evaluation. Classified as SAE with mandatory immediate DSMB notification.

e. Aspiration pneumonia: new radiological infiltrates consistent with aspiration pneumonia occurring within 24 h of pectin administration and judged by the investigator as potentially related to altered gastric viscosity.

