Causality will be assessed by the site investigator using the WHO five-category classification (Certain/Probable/Possible/Unlikely/Unrelated); events judged Possible or above are included in the safety analysis. A SAE is defined as any event resulting in death, life-threatening condition, prolonged hospitalization, or persistent significant disability. Non-serious AEs will be documented in the eCRF within 24 h of detection. SAEs will be reported to the ethics committee and DSMB in accordance with regulatory requirements.

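### The DSMB's list of pre-specified SAEs does not match the adverse event definitions, so non-serious cases of the pectin-specific events may be left out of its scheduled reviews

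*Protocol article*

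**What the plan says.** Section 2.8 (Data and safety monitoring) sets the timing: "The DSMB will conduct safety reviews after every 50 participants complete the intervention". It sets the content in the same sentence: "focusing on cumulative incidence of pre-specified SAEs, including intestinal ischemia, severe abdominal distension, and aspiration pneumonia and etc".

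Section 2.9 (Adverse events) grades all adverse events by NCI-CTCAE v5.0. It then lists five items, a to e, as "the following pectin-specific adverse events of interest, which will be actively monitored throughout the intervention period": abdominal distension, tube obstruction, ileus, intestinal ischemia and aspiration pneumonia. Only intestinal ischemia carries a seriousness label: "Classified as SAE with mandatory immediate DSMB notification". Distension is entered as "Abdominal distension: clinical diagnosis based on physical examination and/or intra-abdominal pressure (IAP) ≥ 12 mmHg on routine bladder pressure measurement", which the text equates with Grade I intra-abdominal hypertension. Aspiration pneumonia is defined as "new radiological infiltrates consistent with aspiration pneumonia occurring within 24 h of pectin administration and judged by the investigator as potentially related to altered gastric" (the last word of that sentence, naming viscosity, is left off here).

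The same section gives the general rule: "A SAE is defined as any event resulting in death, life-threatening condition, prolonged hospitalization, or persistent significant disability". SAEs are reported to the ethics committee and the DSMB. For non-serious events the only stated route is entry in the eCRF within 24 h of detection.

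**The concern.** Section 2.8 treats three events as already specified to be SAEs, but for two of them Section 2.9 contains no such specification. Anyone preparing the DSMB report therefore has two rules to choose from. One is to count every recorded case of the named events. The other is to count only the cases that also meet the outcome-based SAE definition. The two rules can give different cumulative incidences from the same data, and the ten centers may classify similar cases differently.

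This matters because the trial is open-label and has no planned interim efficacy analysis, so the DSMB reviews are its scheduled check on harm. The events most directly tied to a gelling supplement are distension, tube obstruction, ileus and aspiration. If non-serious cases of these are not tabulated, a DSMB record without concerns would say less about those risks than readers would assume.

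**Working it through.** The plan states no figure on this point, so there is none to reproduce. The check sets the two sections side by side.

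| Event of interest (Section 2.9) | Named for DSMB review in Section 2.8? | SAE by designation in Section 2.9? |
|---|---|---|
| a. Abdominal distension | Only if severe | No; one entry threshold, no severe level |
| b. Tube obstruction | No | No |
| c. Ileus | No | No |
| d. Intestinal ischemia | Yes | Yes, with immediate DSMB notification |
| e. Aspiration pneumonia | Yes | No |

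1. *Designation.* One of the five events is an SAE by its own definition. The other 5 − 1 = 4 become SAEs only when the individual case meets the general definition.

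2. *Mismatch with the DSMB list.* Section 2.8 names three events as pre-specified SAEs. Section 2.9 designates one of them, so 3 − 1 = 2 (severe distension and aspiration pneumonia) are called SAEs in one section and not in the other.

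3. *Severity.* Section 2.8 asks for severe distension. Section 2.9 gives a clinical diagnosis and/or a Grade I pressure threshold. CTCAE grades exist for all adverse events, but no grade is tied to the word severe.

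4. *Events not named.* Tube obstruction and ileus are in Section 2.9 but not in Section 2.8. They could enter the reviews only through the open ending of that list, or as individual cases that qualify as SAEs.

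5. *Route for non-serious cases.* Consider a case of distension or aspiration pneumonia that interrupts gastric feeding but is not fatal, life-threatening or disabling. It is an SAE only if it is judged to have prolonged the hospital stay. That is hard to judge in a newly admitted ventilated patient with no planned discharge date. If it is not judged so, the stated route ends at the eCRF. Nothing says whether the DSMB tables are built from the eCRF or from the SAE reports.

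6. *How often this recurs.* Section 2.1 states: "The trial will enroll 212 critically ill adult patients from ten intensive care units (ICUs) across China". With a review after every 50 completers, 212 / 50 = 4.24, so there are up to four scheduled reviews (at 50, 100, 150 and 200). The same ambiguity applies to each.

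7. *Separate minor point.* The general definition counts prolonged hospitalization only. Table 2 schedules adverse events on Days 1 to 7 and at Day 28, so a readmission after discharge falls inside follow-up but does not meet that criterion as worded.

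**The case against.** The strongest reply is that Section 2.8 itself puts severe distension and aspiration pneumonia before the DSMB and, by calling them pre-specified SAEs, arguably designates them. Aggregate review under Section 2.8 is also distinct from case reporting under Section 2.9. Section 2.9 says SAEs go to the DSMB; it does not say that nothing else may. The list in Section 2.8 is open-ended, so obstruction and ileus are not excluded. Seriousness need not be settled at onset, because patients are followed to Day 28. CTCAE supplies a severity scale. Detailed DSMB table content is often left to a charter or a full protocol.

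Much of this stands, and it limits the point. A reader might infer that intestinal ischemia is the only event that can be an SAE. The document does not say so: the general definition applies to any event, and ischemia is only the one that qualifies automatically. A reader might also infer that most of the other events never reach the DSMB, or that the incidence it sees will be near zero whatever the true rate. Neither follows, since no event rates or proportions serious are given and Section 2.8 names two of the disputed events for every review.

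The reply does not remove the conflict. It depends on choosing the broader of two available readings, and an open-ended list is not a pre-specification. Nor is this detail that the article leaves to another document: it states both the DSMB's focus and the event definitions, and they disagree.

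**Conclusion.** The point holds as an inconsistency between stated rules. Two of the three events that Section 2.8 calls pre-specified SAEs are not designated as such in Section 2.9, severe distension is undefined, and two of the five monitored events are not named for DSMB review. Read literally, cases outside the outcome-based SAE definition may be left out of up to four scheduled reviews. This rests on taking SAE in Section 2.8 in the sense defined in Section 2.9. On the broader reading, the named events are counted whatever their seriousness, but the gaps over severity and over obstruction and ileus remain. The number of cases affected cannot be derived from the document. The correction is worth making because the scheduled reviews are the trial's main safeguard and the change is small. The hospitalization wording is a lesser, separate matter.

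**What to change.** Reconcile Sections 2.8 and 2.9 as follows.

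- In Section 2.8, replace the open-ended list with all five events a to e. Tabulate them for each scheduled review from the eCRF by CTCAE grade, regardless of seriousness.
- Tabulate by arm where the definition can apply to both arms. Event e is tied to pectin administration and to a judgement about gastric viscosity, so it needs an arm-neutral definition first. The general adverse event definition also refers to participants receiving the investigational intervention, so state that the events are recorded in controls too.
- In Section 2.9, state which events are SAEs by designation, and use the same list in Section 2.8.
- Tie severe abdominal distension to a stated CTCAE grade, chosen by the trial team.
- Separately, word the hospitalization criterion as new or prolonged hospitalization.

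The cost is protocol and DSMB table wording and slightly longer tables. Adverse events are already entered in the eCRF, so little new data collection is expected, apart from whatever the arm-neutral definition of event e requires in controls.
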